### Sample size {14}

For phase 1, a sample size of *n* = 72 will allow us to detect a small magnitude change (*f* = 0.15) in our primary outcome measure—the standard deviation of lateral position—with 90% power assuming one group (i.e. all patients collapsed into a single group), six repeated measurements (three drives over 2 days), an estimated correlation among repeated measures of 0.6, and a non-sphericity correction of 0.6. The effect size used for this power calculation was derived from a previous on-road driving study with synthetic THC (dronabinol) [15] and conservatively reduced to account for the fact that treatment effects associated with prescribed medical cannabis may be considerably smaller than those seen previously in healthy volunteers given an intoxicating dose of THC. For phase 2*,* a sample size of *n* = 24 will allow us to detect a medium effect size (*f* = 0.25) with 90% power assuming one group, 12 repeated measurements (12 drives over 4 days of testing), an estimated correlation among repeated measures of 0.5, and a non-sphericity correction of 0.6. This effect size (*f* = 0.25) is equivalent to the level of impairment considered meaningful in a recent meta-analysis of 80 publications comprising 1534 driving or cognitive performance outcomes [13]. All sample size calculations were done in G*Power 3.1.

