### Participant timeline {13}

#### Phase 1

In phase 1, patients will first complete a practice session and a baseline drive before completing two separate days of testing, including one test day at AARC and one test day at METEC. Due to the remote location of the AARC test track, participants will be transported by the research team and will stay in a hotel for 2 nights either side of the AARC test day. The test day schedule (see Fig. 1) will be identical for the two test days at AARC and METEC. Patients will complete three 20-min assessments of real-world driving performance over the course of each test day: one assessment (drive 1) prior to medical cannabis self-administration and two assessments (drives 2–3) after medical cannabis self-administration to assess acute effects. The timing of drives 2 and 3 will differ slightly depending on the route of administration to account for differences in cannabinoid pharmacokinetics and, by extension, the typical time course of expected behavioural effects (i.e. onset of effects, time to peak effects, and duration of effects).

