#### Driving performance metrics

The primary outcome measure for both phases of the trial is the standard deviation of lateral position (SDLP), a measure of lane weaving, swerving, and overcorrecting that is highly sensitive to alcohol and drug effects and is widely considered to be the gold-standard measure of driving performance in human psychopharmacology research [22–24]. SDLP and all secondary driving performance metrics are described below in Table 1. The analysis metric is change from pre-dosing to post-dosing (i.e. t2–t1 and t3–t1) for all measures.

**Table 1 Tab1:** Description of driving performance outcome measures

Domain	Measure	Outcome(s)
Driving performance (objective)	Standard deviation of lateral position (primary outcome)	Standard deviation of vehicle lateral position in centimetre (mean)
	Number of lane excursions	Number of times (count) one or more vehicle wheels exceeds the lane boundary
	Speed adherence	Mean speed (km/h) during driving, standard deviation of speed (km/h), and % time above the speed limit
	Steering variability	Steering reversal rate (number of directional changes per minute) and steering entropy (standard deviation of steering angle)
	Harsh acceleration	Count of rapid longitudinal acceleration events where acceleration is ≤ 0.35 g and < 0.58 g (harsh) or ≥ 0.58 g (very harsh)
	Harsh braking	Count of harsh braking events where deceleration is ≤ −0.75 g (extremely harsh), < −0.75g and ≤ −0.5g (very harsh) or ≤ −0.45g (harsh)
Ocular behaviour	Gaze behaviour (entropy)	Stationary gaze entropy and gaze transition entropy
	Rate and duration of visual fixations	Number of fixations (count per minute) and time of fixations (ms) where driver holds their gaze at a specific point on the roadway
	Microsleeps	Frequency (count) of long eye closures lasting ≥ 500 ms (NB: also adverse event indicator)
Driving performance (adverse event)	Instructor termination of drive	Number of times (count) a drive was terminated by the driving instructor
	Instructor intervention during drive	Number of times (count) the driving instructor had to intervene during a drive
Driving performance (subjective)	Instructor rating of fitness to drive	Instructor rating of fitness to drive (yes/no) at the end of each drive (proportion)

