### Statistical analysis {20a, 20b, 20c}

Participant demographic and baseline characteristics will be summarised separately by study phase and treatment condition, where applicable. Continuous variables will be summarised using means and standard deviations (SD), and where appropriate, medians and interquartile ranges (IQR) will also be reported. Categorical variables will be summarised using frequencies and percentages (%). No formal hypothesis testing of demographic variables will be conducted; summaries are intended to describe the study population and assess baseline comparability across groups. Analysis of primary and secondary outcome measures will be conducted using a series of linear mixed-effects models (continuous data), Poisson or negative binomial generalised linear mixed models (count data), logistic mixed-effects models (binary data), or time-binned mixed models and linear regression (ocular data). Post hoc tests with Bonferroni adjustments will be conducted where significant main effects or interaction effects are observed. No deletion or imputation will be used where data is missing at random, as mixed models inherently accommodate incomplete repeated measures. Sensitivity analysis will be conducted using delta-adjustment for nonrandom missing data. Exploratory subgroup analyses will test for differences in change in outcome measures over time as a function of health condition, route of administration, and gender (phase 1 only). All statistical analyses will be conducted using SPSS (IBM Corp, Armonk, NY, USA) and R, and tests will be set two-tailed with a conventional level of significance of *p* < 0.05.

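### The stated 90% power belongs to a test across all 6 (or 12) drives with both tracks mixed, not to the pre-to-post SDLP change or the alcohol–placebo comparison

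*Protocol article*

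**What the plan says.** Sample size {14} states that "a sample size of *n* = 72 will allow us to detect a small magnitude change (*f* = 0.15) in our primary outcome measure", "with 90% power assuming one group (i.e. all patients collapsed into a single group", using "six repeated measurements (three drives over 2 days), an estimated correlation among repeated measures of 0.6, and a non-sphericity correction of 0.6". Phase 2 (n = 24, f = 0.25, 90% power) assumes "12 repeated measurements (12 drives over 4 days of testing), an estimated correlation among repeated measures of 0.5" and the same non-sphericity correction of 0.6. All calculations are attributed to G*Power 3.1; the G*Power test is not named.

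Participant timeline {13} shows what the six Phase 1 measurements are. The two test days are on different circuits, "including one test day at AARC and one test day at METEC", and each day has "one assessment (drive 1) prior to medical cannabis self-administration and two assessments (drives 2–3) after medical cannabis self-administration to assess acute effects".

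The section on driving performance metrics then fixes what is compared: "The analysis metric is change from pre-dosing to post-dosing (i.e. t2–t1 and t3–t1) for all measures". Trial design {8} gives the aim of Phase 2 as the effect of alcohol relative to placebo. Statistical analysis {20a, 20b, 20c} plans mixed models, two-tailed at 0.05, and adds: "Post hoc tests with Bonferroni adjustments will be conducted where significant main effects or interaction effects are observed".

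**The concern.** The sample-size section presents f as a drug effect. The Phase 1 value is derived from a dronabinol driving study and reduced; the Phase 2 value is tied to a meaningful level of impairment. The calculation, however, takes every drive as one level of a single factor, and its null hypothesis is that all 6 (or 12) drive means are equal. That null is also false when highway and urban driving merely differ in SDLP, and it does not separate pre-dose from post-dose drives or alcohol from placebo.

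A reader of the article will take 90% as the chance of detecting a cannabis or alcohol effect on the declared metric. The article gives no such figure. Phase 2 matters most here, because it is the external reference against which the Phase 1 result is to be read.

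**Working it through.** **1. The plan's own figures.** The G*Power within-factors formula (default effect-size option) has λ = f²·n·m·ε/(1−ρ), df1 = (m−1)ε and df2 = (n−1)(m−1)ε, with α = 0.05.

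- Phase 1: λ = 0.15² × 72 × 6 × 0.6/0.4 = 14.58; df 3 and 213; power 90.3%. The smallest n reaching 90% is 72 (n = 71 gives 89.9%).
- Phase 2: λ = 0.25² × 24 × 12 × 0.6/0.5 = 21.6; df 6.6 and 151.8; power 94.1%. The smallest n is 21, so the stated 90% is met with room to spare but is not an exact match.

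For Phase 1, the alternatives tried (m = 2; m = 3; ε = 1; the SPSS and Cohen effect-size options) do not return 90% at n = 72. The one-factor test over six drives is therefore inferred from the inputs and the exact match.

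**2. What that test responds to.** If highway and urban means differ by 0.30 SD and nothing else differs, the six means lie ±0.15 SD from their average, which is f = 0.15. The test rejects with 90% power in the absence of any drug effect.

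**3. Converting f to a drive effect (assumption).** Suppose f comes only from post-dose shifts of size d.

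- Phase 1, pattern (0, d, d) on both tracks: the standard deviation of the six means is d√(2/9) = 0.471d, so d = 0.15/0.471 = 0.318 SD.
- Phase 2, shift at both post-alcohol drives on both tracks: d = 0.25/0.471 = 0.53 SD. Shift at drive 2 only: the standard deviation is d√(5/36) = 0.373d, so d = 0.67 SD. The simple two-mean conversion d = 2f gives 0.50 SD.

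**4. Phase 1 power for t2–t1.** Under compound symmetry the change on one track has variance 2(1−ρ); averaging two tracks halves it. Paired t test, n = 72, d = 0.318:

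| ρ | One track, α 0.05 | Tracks pooled, α 0.05 | Tracks pooled, α 0.025 |
|---|---|---|---|
| 0.6 | 85% | 99% | 97% |
| 0.5 | 76% | 96% | 93% |

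**5. Phase 2 power for the alcohol-minus-placebo difference in t2–t1.** The variance on one track is 4(1−ρ) = 2 at ρ = 0.5; pooled over two tracks it is 1. Paired t test, n = 24, α = 0.05:

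| d (SD) | One track | Tracks pooled |
|---|---|---|
| 0.50 | 38% | 65% |
| 0.53 | 42% | 70% |
| 0.67 | 60% | 88% |

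**6. Sensitivity to the correlation structure.** If drives on the same day correlate at ρs and drives on different days share a constant correlation, the pooled variance in step 5 becomes 2(1−ρs). For d = 0.53–0.67, power is 79–94% at ρs = 0.6, 89–98% at 0.7 and 98–99.9% at 0.8.

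**7. Detectable effects at 90% power, tracks pooled, t2–t1.** At α = 0.05: Phase 1, 0.245 SD (ρ = 0.6) to 0.274 SD (ρ = 0.5); Phase 2, 0.69 SD (ρ = 0.5). At α = 0.025 the same formulas give 0.267–0.299 SD and 0.76 SD.

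**The case against.** The strongest reply is that the G*Power entry is a planning simplification, not the analysis. The analysis section speaks of main effects and interaction effects, which implies more than one factor. With track and drive as separate terms, a highway–urban difference falls on track, and change from drive 1 removes any constant track difference. This stands: the article does not show that the trial will gate its results on a six-level test, and the 0.30 SD example concerns the power calculation only. The exact model terms may also sit in an analysis plan that is not shown.

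A second reply is that Phase 1, which carries the primary aim, loses nothing. With tracks pooled this also stands (step 4). The lower figures need one track tested alone, which no section makes primary, although no section says that tracks are pooled either.

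A third reply is that the Phase 2 shortfall rests on compound symmetry, whereas the article's own non-sphericity value of 0.6 departs from it. This stands in part. Step 6 shows that a higher same-day correlation can bring power to 90% or above, and a treatment-by-drive interaction test on both tracks at 0.67 SD reaches 92% with ε = 1. But the article states no such correlation structure.

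None of these replies turns the stated 90% into the power of the declared comparisons.

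**Conclusion.** The point holds as a mismatch between the stated power and the comparisons that the trial declares. The Phase 1 arithmetic is correct, but for a different hypothesis. That it is the one-factor test is inferred from the inputs, firmly for Phase 1 and less so for Phase 2, where the formula gives 94% rather than 90%.

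The size differs by phase. In Phase 1 the pooled t2–t1 contrast has 96–99% power at 0.318 SD. In Phase 2 the alcohol–placebo difference in t2–t1 has about 65–88% pooled and 38–60% on one track. That range rests on ρ = 0.5, compound symmetry and the conversions of f in step 3.

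Two stronger readings are tempting and are not supported. One is that Phase 1 is underpowered; that would need single-track testing, which is not planned as primary. The other is that different correlations in the two phases (0.6 and 0.5) are an error. The phases differ in population, number of days and treatments, so different values are a legitimate planning choice, though Phase 1's one-factor power would be 82% at 0.5 (λ = 11.66).

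**What to change.** Rewrite the sample-size paragraph to give power or detectable effect for the declared contrasts: t2–t1 and t3–t1 in Phase 1, and the alcohol-minus-placebo difference in those changes in Phase 2. State that the primary SDLP test pools the two tracks with track as a fixed effect, and state the correlation assumed, separating same-day from between-day correlation if they are thought to differ. For t2–t1, the step 7 figures can be used: about 0.245–0.274 SD in Phase 1 and 0.69 SD in Phase 2 at α = 0.05, or the α = 0.025 values if the adjustment below is applied.

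In the analysis section, test the two declared contrasts directly, with Bonferroni over those two, instead of only as post hoc tests that depend on a significant overall effect. Phase 1 keeps about 93–97% power for t2–t1 at 0.318 SD. Both contrasts can stay as declared.

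The cost is one paragraph and one analysis sentence, with no extra participants. The downside is a less favourable Phase 2 figure. Recruitment is expected to end in mid-2026, so the change should be recorded before outcome data are examined.

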### Recruitment {15}

Participants will be recruited through dedicated practitioner channels, cannabis clinics in Melbourne, word o -mouth, and official recruitment streams (printed and online advertisements).

### Interventions {11} and allocation {16a, 16b, 16c, 17a, and 17b}

#### Phase 1

Patients will self-administer a standard dose of their prescribed cannabinoid medication at the time specified in the test day schedule (see Fig. 1). Self-administration will be witnessed by the study nurse who will confirm that the dose administered is consistent with instructions on the pharmacy label. In the case that patients report using more than one cannabinoid medication, they will be asked to use the medication that they would be most likely to use at that time of day, as patients often report using different types of cannabinoid products during the day and at night. Patients who would not normally take their cannabinoid medication during the day (e.g. patients with a sleep disorder) will be asked to use whatever their primary cannabinoid medication is, noting that the primary aim here is to assess the acute effects of that medication and that it would be impossible to organise test sessions around patients’ individual medication schedules.

#### Phase 2

Participants will be administered placebo or alcohol to achieve a target BAC of 0.05%, with an expected peak at 30–45-min post-ingestion. This will be achieved using an adjustable calculation based on the Widmark formula. Widmark’s formula states that one’s blood alcohol content is equal to the number of ounces of alcohol consumed, multiplied by a constant—for men by 3.75 and for women by 4.70—and then divided by that person’s weight. The formula is as follows: BAC = [alcohol consumed in grams/(body weight in grams × R)] × 100. For an average of 70-kg male person to achieve 0.05% BAC, this will require dosing of ~100 g of 40% alcohol or 3.7 standard drinks (30mL shots) with 201-g mixer orange juice (total drink 302 g). Placebo will be non-alcoholic vodka and orange juice, which we have effectively used to blind participants in previous studies. Non-alcoholic vodka is a clear, colourless liquid that is flavoured and formulated to mimic the taste and aroma of traditional vodka but contains no alcohol. Treatments will be prepared by the unblinded study nurse and given to participants in a stainless-steel mug with a lid and a straw to minimise potential unblinding during treatment administration. Allocation to treatment order (alcohol/placebo) will be randomised and counterbalanced according to a randomisation schedule held by the nurse and the study medical doctor. In the case of a serious adverse event occurring, emergency unblinding will be performed by the study nurse.

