### Trial design {8} and choice of comparators {6b}

We will conduct a two-phase trial to assess the effects of medical cannabis and alcohol on real-world driving performance. Phase 1 is a semi-naturalistic trial in which patients will complete driving assessments at two separate closed-circuit tracks (highway/urban driving environments) before and after consuming a standard dose of their prescribed cannabinoid medication. We decided not to institute a placebo control for patients as it was deemed unethical to withhold a patient’s treatment and because adequate blinding would be near impossible. In the absence of a placebo control for patients, we will implement an external control in the form of a secondary study (phase 2): a randomised, double-blind, placebo-controlled trial in which healthy volunteers will complete the exact same assessments at the same two tracks before and after consuming either alcohol (0.05% BAC) or placebo. Alcohol was chosen as the external control intervention for two reasons: (1) given the wide range of cannabinoid medications that we expect patients to be using, it would be impossible to select a ‘comparable’ dose or formulation for each participant and (2) because the dose to be administered is equivalent to the legal threshold for drivers in Australia (and numerous other countries) and thus has real-world relevance for road safety.

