### Eligibility criteria {10}

#### Phase 1

For patients, inclusion criteria are as follows: (1) current medical cannabis prescription for chronic pain, anxiety, or insomnia persisting > 6 months, (2) on a stable dose of medical cannabis (≥ 3 months) with≥ 2 mg of THC/dose, (3) aged > 21 years, (4) in possession of a current and unrestricted Victorian driver licence, and (5) able to consume medical cannabis during the day as required for testing. Exclusion criteria are as follows: (1) On an unstable dose of medical cannabis or dose titrating, (2) unstable use of other medications that could impair driving, (3) unable to attend the test facilities for full-day testing sessions and stay overnight in a hotel for 2 nights, and (4) pregnant or lactating.

#### Phase 2

For healthy volunteers, inclusion criteria are as follows: (1) previous history of alcohol consumption in a single drinking session to an estimated BAC of 0.05% with no known adverse reaction [more than two standard drinks (female) or three standard drinks (male) on a single occasion], (2) under 100 kg (for weighted alcohol dose), (3) aged > 21 years and in possession of an unrestricted driver’s licence, and (4) oral fluid negative for all illicit drugs on the morning of test sessions. Exclusion criteria are as follows: (1) Use of cannabis > 1×/week; (2) AUDIT score (> 12) indicating problematic drinking; (3) use of any psychoactive medication that could impact driving; (4) current diagnosis of any Axis 1 mental health or substance use disorder; (5) taking any form of medication within 1 week of admission (except for routine medications to treat benign conditions); (6) unable to participate in scheduled visit, treatment plan, test, and other study procedures according to the protocol; (7) moderate-severe current depression (Beck Depression Inventory score of ≥ 20); (8) severe current anxiety (Beck Anxiety Inventory score of ≥ 16); (9) current participation in any other studies involving investigational or marketed products within 30 days prior to the screening visit; and (10) currently under administrative or legal supervision.

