**Fig. 1 Fig1:**
[figure not shown]
SPIRIT figure — schedule of enrolment, interventions, and assessments

For patients using oral products (*n* = 36), drive 1 will occur prior to medical cannabis self-administration, with drives 2 and 3 occurring 1.25 and 3 h after medical cannabis self-administration. For patients using inhaled products (*n* = 36), drive 1 will occur prior to medical cannabis self-administration, with drives 2 and 3 occurring 0.5 and 2.25 h after medical cannabis self-administration. Informed by prior work [13], drives 2 and 3 both fall within the potential window of impairment associated with inhaled and orally administered THC, with drive 2 corresponding to the expected period of peak effects, when impairment—if present—is likely to be greatest [14]. Blood and oral fluid samples will be collected immediately prior to each drive. An impairment assessment battery comprising cognitive testing and subjective drug effect questionnaires (see Outcomes {12}) will be administered immediately following each drive.

#### Phase 2

In phase 2, participants will first complete a practice session and a baseline drive before completing four separate days of testing, including two test days at AARC and two test days at METEC. Due to the remote location of the AARC test track, participants will be transported by the research team and will stay in a hotel for 2 nights before each of the two AARC test days before being transported back to Melbourne on the afternoon of the second AARC test day. Participants will then, in that same week, complete the two test days at METEC. Given the considerable logistical complexities associated with testing at remote locations, and to minimise potential dropouts, test days will be scheduled to occur back to back, meaning the washout period between test days will be minimal but within the expected metabolic elimination window for acute low doses of alcohol. As in phase 1, participants will complete three driving assessments within each test day, including a baseline drive in the morning (drive 1) followed by a second drive at the time of expected peak alcohol impairment (drive 2) and a third drive when impairment is expected to be subsiding (drive 3). The test day schedule (see Fig. 1) will be identical for each of these four testing days. The order in which participants receive alcohol and placebo at the two tracks will be randomised and counterbalanced.

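### The worked alcohol dose for a 70-kg man does not follow from the dosing formulas printed beside it

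*Protocol article*

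**What the plan says.** The Phase 2 part of the Interventions section sets a target BAC of 0.05%, expected to peak 30 to 45 minutes after drinking. The dose comes from "an adjustable calculation based on the Widmark formula"; the adjustment is not described. Three statements follow.

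- An ounce rule: ounces of alcohol multiplied by a constant ("for men by 3.75 and for women by 4.70") and divided by weight, with no unit for weight and no type of ounce.
- A gram formula: "BAC = [alcohol consumed in grams/(body weight in grams × R)] × 100", with no value for R.
- A worked case for a 70-kg man: "to achieve 0.05% BAC, this will require dosing of ~100 g of 40% alcohol or 3.7 standard drinks (30mL shots"). The spirit is then made up to a full drink, given as "with 201-g mixer orange juice (total drink 302 g").

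Elsewhere, the Trial design section justifies the comparator partly because "the dose to be administered is equivalent to the legal threshold for drivers in Australia". The Participant timeline places "a second drive at the time of expected peak alcohol impairment (drive 2"). The Eligibility criteria associate an estimated 0.05% with "more than two standard drinks (female) or three standard drinks (male) on a single occasion".

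**The concern.** The section presents the ounce rule and the gram formula as the same Widmark calculation and then gives the dose that is meant to result. A reader who puts 70 kg and 0.05% into either one, as printed, does not arrive at that dose by any ordinary choice of units or R.

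The alcohol arm is the external reference for phase 1, and its meaning rests on the claim that the dose corresponds to the legal threshold. The Objectives section notes that readings up to 0.049% are lawful, so a modest shift in achieved BAC changes what the reference stands for. If the dose cannot be rebuilt from the text, a reader cannot tell what level was aimed at in practice.

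**Working it through.** **Inputs from the article:** target 0.05%; 70 kg; 100 g of 40% spirit; 302 − 201 = 101 g of spirit from the drink weights; 3.7 × 30 mL = 111 mL; male constant 3.75; peak at 30 to 45 minutes.

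**Assumed, not in the article:** ethanol density 0.789 g/mL; density of 40% v/v spirit 0.948 g/mL; male R 0.60 to 0.75; elimination 0.01 to 0.02% per hour.

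**1. Ethanol in the worked drink**
- 100 g: 100/0.948 × 0.40 × 0.789 = 33.3 g
- 101 g: 33.6 g
- 3.7 shots: 111 × 0.40 × 0.789 = 35.0 g

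The two stated amounts differ by 35.0/33.3 = 1.05. Equivalently, 100/0.948/30 = 3.52 shots.

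**2. Gram formula as printed**

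Dose = 0.0005 × 70,000 × R = 35.0R g. The R needed is 33.3/35.0 = 0.95, 33.6/35.0 = 0.96 or 35.0/35.0 = 1.00. Other readings of the example are 100 mL of spirit (31.6 g, R = 0.90) and 40% by weight (40 g, R = 1.14).

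**3. Ounce rule for men, no allowance**

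Ounces = 0.05 × weight/3.75, which is 0.933 oz with weight in kg (70) or 2.058 oz with weight in lb (154.3). Grams of ethanol:

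| Reading of an ounce | kg | lb |
|---|---|---|
| Ethanol, US fluid | 21.8 | 48.0 |
| Ethanol, UK fluid | 20.9 | 46.1 |
| Ethanol, by weight | 26.5 | 58.3 |
| 40% spirit, US fluid | 8.7 | 19.2 |
| 40% spirit, UK fluid | 8.4 | 18.5 |
| 40% spirit, by weight (v/v) | 8.8 | 19.4 |
| 40% spirit, by weight (w/w) | 10.6 | 23.3 |

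Nothing falls between 26.5 and 46.1 g, so none gives 33 to 35 g, nor even the wider 31.6 to 40 g.

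**4. Adding an elimination allowance**

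The assumed rates over 0.5 to 0.75 h give 0.01 × 0.5 = 0.005 to 0.02 × 0.75 = 0.015 percentage points, so the formula would aim at 0.055 to 0.065%.
- Gram formula: the example fits at R from 33.3/(0.00065 × 70,000) = 0.73 to 35.0/(0.00055 × 70,000) = 0.91.
- Ounce rule, kg with weight ounces of ethanol: 26.5 × 1.1 to 26.5 × 1.3 = about 29.1 to 34.4 g. This covers 100 to 101 g of spirit but not 3.7 shots (35.0 g).
- The other ounce readings still miss. The next largest below the example rise to at most 23.3 × 1.3 = 30.3 g and 21.8 × 1.3 = 28.3 g, and those at 46.1 g or more only move further away.

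**5. What the example would deliver at R of 0.60 to 0.75**
- 33.3 g: from 33.3/(70,000 × 0.75) × 100 − 0.015 = 0.048% to 33.3/(70,000 × 0.60) × 100 − 0.005 = 0.074%
- 35.0 g: from 0.0667 − 0.015 = 0.052% to 0.0833 − 0.005 = 0.078%

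To hit 0.05% exactly, the built-in allowance would have to be 0.013 (33.3 g, R = 0.75) to 0.033 (35.0 g, R = 0.60) percentage points. This overlaps the assumed 0.005 to 0.015 only at its low end.

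**The case against.** The best defence is that the calculation is called adjustable. With an elimination allowance the gram formula can reach the example at a plausible R, and one reading of the ounce rule covers the weighed amount. This stands: it would be wrong to say that the three statements can never be reconciled. But the allowance is not printed, the ounce reading that works mixes kilograms with ounces, and no allowance makes 100 g equal to 3.7 shots. The approximation sign on the 100 g softens that last mismatch without removing it.

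A second defence is that R and the dosing sheet belong in the full protocol. That is fair, and the missing value of R is not the point. The point is that the figures that are printed do not follow from one another.

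A reader might go further. Since 3.7 shots hold 35.0 g, exactly 0.05% of 70 kg, one could infer that R was dropped and everyone gets a flat 35.0/70 = 0.50 g/kg. By the printed constants, women would then reach 4.70/3.75 = 1.25 times the BAC of men. The documents do not support this. The near-exact match needs the shot count and assumed densities, and the gram amounts give 0.95 to 0.96. The article also prints sex-specific constants and sex-specific drink counts. The criterion of more than three drinks for men agrees in direction with 3.7.

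Finally, breath readings are taken through the day and will show the BAC reached. That limits the damage, but only after dosing.

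**Conclusion.** The concern holds as a fault in the stated dosing rule: the printed dose does not follow from the printed formulas without an adjustment that the text does not give, and its two spirit amounts disagree by about 5%. It does not show that the dose is wrong, or in which direction. The range of about 0.048 to 0.078% includes the target and lies mostly above it, but rests on assumed values of R, elimination rate and densities. The randomised alcohol-placebo comparison stays valid at whatever BAC is reached. What is exposed is the label of 0.05% on the reference for phase 1. Severity is minor to should-fix.

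**What to change.** - State one gram formula, with R by sex and an explicit elimination allowance, and delete the ounce rule.
- Recompute the 70-kg example from that formula and give a single spirit amount. Change the dose only if it does not reproduce.
- Before any further dosing, check the dosing sheet against the formula, including that R is applied and differs by sex. If dosing is complete, report the doses given.
- When setting phase 2 beside phase 1, describe the alcohol reference by the measured breath BAC around drive 2, not by the nominal 0.05%. Keep the randomised contrast as it is.

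The cost is one corrected paragraph and one check of a sheet. No new data are needed, because breath BAC is already collected and summarised by timepoint. The Trial status section expects recruitment to end in mid-2026, so the check may still precede the last dosing days.
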